### Study objectives and outcomes

The primary objective of the ALCAT trial is to demonstrate that acetyl-DL-leucine is effective at improving motor function measured by the SARA total score. The primary efficacy endpoint is the absolute change in the SARA total score from period-level baseline to the end of the 6-week treatment period, i.e. the difference between post-treatment values at the end of each treatment period and the corresponding period-level baseline values:$$ \mathrm{Delta}\ \left(\mathrm{SARAtotal}\right) = \mathrm{SARAtotal}\ \left(\mathrm{post}\hbox{-} \mathrm{treatment}\right)\ \hbox{--}\ \mathrm{SARAtotal}\ \left(\mathrm{period}\ \mathrm{baseline}\right) $$

We presume a minimum clinically relevant difference in the SARA total score of 1.5 points. The secondary objectives are to determine whether Acetyl-DL-Leucine is effective at:improving motor function measured by the Spinocerebellar Ataxia Functional Index (SCAFI) and SARA subscore itemsimproving QoL, as well as the common comorbidities depression and fatigue.

The secondary efficacy outcome measures will be absolute changes in the subscores of SARA as well as the SCAFI total score and subscores of SCAFI (8 MW testing gait, 9HPT testing limb ataxia and the PATA rate task for speech). Furthermore, patient-reported outcomes using the EuroQoL 5 dimensions and 5 level version (EQ-5D-5 L), Beck’s Depression Inventory (BDI-II) as well as the Fatigue Severity Scale (FSS) will be recorded.

For all these scores, the treatment effect will be assessed at the end of each treatment period and at the post-treatment follow-up visit.

During the whole study period any AE (any untoward medical occurrence, including an abnormal laboratory finding, regardless of its causal relation to the study treatment) will be recorded.

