### Statistical planning and analyses

#### Power considerations and sample size calculation

The sample size was calculated on the basis of the primary hypothesis, using our own preliminary case series data (13 patients [17]) and a similar placebo-controlled trial (20 patients [7]) investigating the efficacy of varenicline on the change in SARA total score in patients with SCA 3. Hence, assuming a minimum clinically relevant difference in the SARA total score of 1.5 points [25] to be detected (i.e. the absolute change on acetyl-DL-leucine is 1.5 score points better than the change on placebo) and a standard deviation of the individual SARA change of 4.2, a sample size of 86 (85 is calculated but 2 sequences are needed) in total is will have 90% power to detect a difference in means of 1.5, using a paired *t*-test with a 0.05 two-sided significance level [Software used: nQuery Advisor 7.0]. On the basis of our experience with patient compliance in previous studies, we expect a dropout rate of about 20%. Thus, a total of 108 patients have to be enrolled. With a proportion of about 50–55% recruited patients out of the number to be screened, about 200 patients have to be assessed for eligibility. There is no interim analysis planned for this study.

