#### Statistical analyses for primary and secondary endpoints

Efficacy analyses are based on the intention to treat (ITT) principle in that all participants randomized will be analyzed according to the treatment sequences to which they were allocated and irrespective of the extent of intervention received. In this study, the term ‘full analysis set’ is used to describe the analysis set, which is as complete as possible and as close as possible to the ITT ideal of including all randomised participants (i.e, the ITT population). All statistical tests are two-sided, and the significance level alpha is set to 5%.

For the primary efficacy outcome change in SARA total score (DeltaSARA), the null hypothesis will be tested that there is no difference in mean change between placebo and acetyl-DL-leucine.

Absolute change, calculated as the difference between the period-level baseline score and the score measured at the 2-week and 6-week visits of the acetyl-DL-leucine/placebo period, will be considered for a model-based primary efficacy analysis. If not revised in the statistical analysis plan (SAP), a linear mixed effects model for DeltaSARA will be performed (fixed effects: factor for treatment, visit, treatment-by-visit interaction, and mean of both period-level baseline SARA total scores as covariate; normally distributed patient-specific random intercepts and slopes) in order to deal with repeated measurements within periods and measurements not made at equivalent times in each subject due to unscheduled or missed clinic visits. This subject-specific modelling approach allows individual change scores over time to be calculated. To analyse the differences between both interventions at the end of the 6-week treatment period, 95% confidence intervals will be provided to quantitatively describe treatment effects.

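### Read with slopes over time, the default primary mixed model has no patient-by-period variance component, so its type I error can exceed 5% (about 7% at week 6 in the simplest case)

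*Protocol article*

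**What the plan says.** All of this is in the protocol article. *Study objectives and outcomes* defines the endpoint at one time point: "The primary efficacy endpoint is the absolute change in the SARA total score from period-level baseline to the end of the 6-week treatment period". *Statistical analyses for primary and secondary endpoints* then models two changes per period, each "calculated as the difference between the period-level baseline score and the score measured at the 2-week and 6-week visits".

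The fixed effects are treatment, visit, their interaction, and the mean of the two period baselines. The random part is "normally distributed patient-specific random intercepts and slopes) in order to deal with repeated measurements within periods". No patient-by-period effect, residual correlation structure or robust variance is named. The slope variable is not named either, although the same paragraph says the approach gives each patient's change over time. The 95% confidence intervals are tied to the end of the 6-week period. The level is stated as: "All statistical tests are two-sided, and the significance level alpha is set to 5" per cent. The model is a default that stands unless the SAP revises it.

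**The concern.** The week-2 and week-6 changes in one period share that period's baseline, and so share its measurement error and any drift specific to that period. Changes from different periods do not share them. The baseline covariate is the mean over both periods, so it cannot remove an error that belongs to one period.

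Treatment is constant within a period and differs between the two. Its standard error therefore depends on how much a patient varies from period to period. Patient-level intercepts and slopes over within-period time imply the same covariance between the visits of one period as between the same visits of different periods. The unmodelled period-level variance then goes partly into the patient effect, which cancels from the treatment comparison, and partly into an independent residual.

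This is the primary test of a phase III superiority trial, and a significant result opens confirmatory testing of the EQ-5D-5L. If the standard error is too small, the confidence interval is too narrow and a false claim of superiority is more likely than 5%.

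**Working it through.** **The plan's own figure.** *Power considerations and sample size calculation* gives "assuming a minimum clinically relevant difference in the SARA total score of 1.5 points", "a standard deviation of the individual SARA change of 4.2" and "90% power to detect a difference in means of 1.5". The normal approximation is (1.96 + 1.2816)² × 4.2² / 1.5² = 82.4, so 83. The exact paired t-test needs 85 (power 90.2%), and 86 gives 90.6%. Allowing for 20% dropout, 86 / 0.8 = 107.5, so 108. The sample size reproduces and is not affected by this point.

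**Simplest case (assumption).** Every SARA value carries independent error of variance s², and patients do not differ in true change. Within a period, D2 = Y2 − Y0 and D6 = Y6 − Y0.

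- True covariance: Var(D) = 2s², within-period covariance s² (correlation 0.5), cross-period covariance 0.
- Model with slopes over within-period time: an arbitrary 2×2 patient matrix A, common to both periods, plus an independent residual r.
- Take sums and differences of the two periods, each divided by √2. Both truly have eigenvalues 3s² and s². The model gives 2A + rI for the sums and rI for the differences.
- The sums can fit 3s² exactly, but their other eigenvalue cannot fall below r. In units of s², the large-sample fit minimises 3·log r + 5/r, so r = 5/3.
- Fitted within-period correlation: (1/3) / 2 = 0.17, against a true 0.5.

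| Contrast | Model variance | True variance | Level |
|---|---|---|---|
| Week 6 | 2r = 3.33s² | 4s² | 2[1 − Φ(1.96·√(3.33/4))] = 7.4% |
| Average of weeks 2 and 6 | r = 1.67s² | 3s² | 2[1 − Φ(1.96·√(1.67/3))] = 14.4% |

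If 4.2 is the SD of the within-patient difference, as the paired t-test uses it, then s = 2.1. With 86 patients the correct week-6 standard error is 4.2/√86 = 0.453. The model reports 0.453 × √(3.33/4) = 0.413. The half-width of the 95% interval is 0.81 instead of 0.89.

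**Other variance components (all assumed).** Trials with no treatment effect were simulated with 86 patients and fitted by REML. Most settings had 5000–6000 runs without the baseline covariate. Some had 800–1500 runs with it.

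| Setting | Week 6 | Averaged |
|---|---|---|
| Shared baseline only, correlation 0.5 | 7.3–7.4% | 14–15.5% |
| Correlation 0.7–0.8 | 8.4–9.2% | 18–20% |
| Week-2 variance 0.6 of week-6 variance, correlation 0.6 | 7.9–12.4% | 12–17% |
| Moderate patient differences in change, correlation 0.5 | 5.7–6.7% | 12–13% |
| Large patient differences in change, correlation 0.5 | 5.0–5.3% | about 10.5% |
| Independent patient-by-visit effects | 4.8–4.9% | 10.5–11% |
| Slopes over whole-study time | 5.2–8.8% | 8.6–12% |
| Patient-by-period effect added | 5.0–5.8% | 5.6–6.5% |
| Paired t-test on week-6 changes | 4.7–5.2% | – |

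The Monte Carlo standard error in the row for the added effect is about 0.6–0.8 points. As a check, with the within-period correlation set to 0 the planned model rejects in 5.8% for either contrast. A small part of the simulated excess is thus a finite-sample effect unrelated to the shared baseline.

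**The case against.** Four points on the other side carry weight.

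- **The slope variable is undefined.** If it were treatment, the problem would largely go. An intercept variance of s², a treatment-slope variance of 2s² and a covariance of −s² give within-period covariance s² and cross-period covariance 0, which is the true structure. The reference to change over time favours a time slope, but the text does not settle it.
- **A reader might infer that the level must exceed 5%.** The documents do not support that. They give no variance components, and the week-6 excess disappears when patients differ strongly in their change and the two visits have equal variance. That protection is incomplete: with large patient differences but a week-2 variance of 0.8 of the week-6 variance (correlation 0.55), the level is 6.3–6.7%. Equal variances cannot be assumed, since week 2 falls at the end of up-titration.
- **A reader might take 14% or more as the error of the primary test.** That is not supported. The endpoint definition, the treatment-by-visit term and the confidence intervals at the end of the period together point to week 6. The averaged figures apply only if the treatment factor were tested over both visits, which the statement of the null hypothesis does not expressly exclude.
- **The SAP may revise the model**, and it is not shown. It cannot be said that the confirmatory test will be run this way. But the article does state a specific random-effects structure as the default, so the point concerns what is written, not a detail left out.

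It would also be too strong to say that the two changes in a period are treated as independent: the model recovers about 0.17 of the 0.5 correlation.

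**Conclusion.** The point holds as a conditional one. With slopes over time and the default left unrevised, the primary model lacks the variance component on which the treatment standard error depends, and its level can exceed 5%.

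For the week-6 contrast the level is about 7% in the simplest case. It is about 5% when patients differ strongly in their change, about 8–9% when the within-period correlation is higher, and up to about 12% when variance grows between weeks 2 and 6. For a visit-averaged test it would be about 14% in the simplest case and roughly 9–20% across the settings examined. All of these figures rest on assumed variance components. The mechanism follows from the model as written; the size does not.

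**What to change.** Before unblinding, in the SAP:

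1. Add a patient-by-period random intercept alongside the patient effect, or fit an unstructured 2×2 covariance for the two visits within each period, nested in patient.
2. State which variable the random slopes refer to.
3. Name the week-6 treatment contrast, which matches the endpoint definition, as the single primary test.

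The cost is SAP wording and a small change to the model code. No new data are needed. The confidence interval becomes somewhat wider (in the simplest case a half-width of 0.89 instead of 0.81 SARA points), which is its correct width.

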### Randomization, concealment, and blinding

Participants fulfilling the entry criteria at screening will be randomly assigned in a ratio of 1:1 to receive one of the two treatment sequences (active treatment followed by placebo, or vice versa). The randomization technique is based on permutated balanced blocks with random block length. The procedure considers stratification by study site and by genetic vs. sporadic CA to ensure balanced strata, maintaining allocation concealment. The allocation sequence will be generated by an independent person from the Institute of Medical Informatics, Biometry and Epidemiology (IBE) of the University of Munich who is not involved in assessing study outcomes. Neither the investigators nor other trial staff (data analysts, statisticians) or the patients will be informed about the treatment sequences to which a patient is allocated, and neither has access to the randomization list. Thus, randomisation will be conducted without any influence of the investigators or trial staff. The IBE will provide an internet-based, password-protected randomization tool (“Randoulette”: https://wwwapp.ibe.med.uni-muenchen.de/randoulette), which chooses the treatment sequence for a new patient who fulfills the eligibility criteria and has signed the informed consent. Randoulette will register the patient by his or her screening number, gender, year of birth and strata before the allocated package number is provided. The current trial is subject— and investigator-blinded. Patients, clinicians, core laboratories, and trial staff (including data analysts and statisticians) will be unaware of the treatment that the participant will take during both double blind treatment periods.

Un-blinding will occur in the event of a clinical emergency in which the knowledge of the medication being taken is essential for the participant’s clinical management. The investigator is supplied with an opaque sealed envelope for each participant that contains the corresponding treatment sequence for unblinding. Alternatively, the randomization code can be broken using Randoulette.

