### Trial procedures and interventions

Each treatment sequence consists of a first treatment period of 6 weeks (42 days), followed by a 4-week (28 days) wash-out period, and a second treatment period of 6 weeks (42 days). Finally, a post-treatment follow-up is scheduled 4 weeks (28 days) after the end of the second treatment period (see fig. 1). The 4-week wash-out period between consecutive treatments is assumed to be long enough to allow the effects of a treatment to wear off and prevent carry over from one treatment period to the next.

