Sensitivity analyses will be performed on a per protocol approach which takes into account treatment adherence and compliance with the trial protocol. Additional efficacy analyses adjusting for genetic vs. sporadic CA, gender, age, or trial site, will be performed. In addition, the robustness of the overall efficacy result will be investigated by analyses adjusting for the amount of physiotherapy the patient received when he or she was enrolled in the trial (which should be comparable to the amount received before randomization), as considered appropriate during the blinded data review and depending on the data quality. Since this analysis will also be based on variables measured after randomization, the susceptibility for bias will be given consideration and will be discussed.

In case of a statistically significant primary efficacy result, confirmatory testing will be extended to the EQ-5D-5 L (VAS and descriptive scale). SCAFI (total score and 3 subscores), SARA subscale items, as well as patient-reported outcomes BDI-II and FSS are not considered in the hierarchical multiple testing procedures. Descriptive comparisons between treatment groups at the end of the 6-week acetyl-DL-leucine/placebo period will be performed using a two-sided Wilcoxon signed rank test, and additionally, Hodges-Lehmann estimation of the location shift between the two groups will be provided, as considered appropriate based on the blinded data. The same non-parametrical tests will be employed to estimate treatment differences at the follow-up visit 8 (close-out visit). Further methodological details will be provided in the SAP.

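### The paired signed-rank test prescribed for treatment differences at visit 8 has no active/placebo pair at that visit; only the descriptive follow-up results are affected

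*Protocol article*

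**What the plan says.** The relevant statements are all in the Protocol article.

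- **Statistical analyses for primary and secondary endpoints.** Descriptive comparisons at the end of the 6-week periods "will be performed using a two-sided Wilcoxon signed rank test", and in addition "Hodges-Lehmann estimation of the location shift between the two groups will be provided". The next sentence carries the method forward: "The same non-parametrical tests will be employed to estimate treatment differences at the follow-up visit 8 (close-out visit". No other non-parametric test is named, and further methodological detail is left to the SAP.
- **Study objectives and outcomes.** For the listed scores, "the treatment effect will be assessed at the end of each treatment period and at the post-treatment follow-up visit".
- **Trial procedures and interventions.** The first period is "followed by a 4-week (28 days) wash-out period" and then the second period; finally, "a post-treatment follow-up is scheduled 4 weeks (28 days) after the end of the second treatment period".
- **Randomization, concealment, and blinding.** Patients are "randomly assigned in a ratio of 1:1" to "one of the two treatment sequences (active treatment followed by placebo, or vice versa".
- **Table 2.** Visit 8 appears once, on day 140. SARA, SCAFI and the three questionnaires are collected at both visit 5 and visit 8.

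**The concern.** A signed-rank test works on within-patient differences. To estimate a treatment difference, each patient must supply one value labelled active and one labelled placebo. Visits 4 and 7 supply these. Visit 8 supplies a single value, taken after the whole sequence.

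An analyst who follows the sentence literally must therefore find a difference somewhere. The ready-made ones are changes over time: visit 8 minus baseline, minus the period 2 baseline, or minus visit 7. Pooled over both sequences, each of these mixes patients last treated with active and patients last treated with placebo. The test then asks whether scores moved over time, from practice, progression, placebo response or anything else, and the answer could be reported as a treatment difference. At stake is the follow-up result for every score assessed at visit 8.

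**Working it through.** **1. Inputs from the document.** Table 2 gives visit 2 on day 0, visit 4 on day 42, visit 5 on day 70, visit 7 on day 112 and visit 8 on day 140. Visit 5 is thus 70 − 42 = 28 days after period 1, visit 8 is 140 − 112 = 28 days after period 2, and visit 8 is 140 − 42 = 98 days after period 1.

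The sample size reproduces. A paired t-test with difference 1.5, SD 4.2 and two-sided alpha 0.05 needs n = 85 for 90% power (power 0.902); 86 is used for two sequences; 86 / 0.8 = 107.5, hence 108. Per sequence this is 86 / 2 = 43 if only the planned completers attend visit 8, and 108 / 2 = 54 if all attend. Attendance at visit 8 is not given, so both are assumptions.

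**2. Values per patient and score.** End of treatment (visits 4 and 7): two values, one per treatment, hence one pair. Visit 8: one value, hence no pair.

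**3. What each contrast estimates.** Let AP and PA be the sequences active–placebo and placebo–active. Let d5 and d8 be the common change from baseline to visits 5 and 8. Let τ be the treatment effect remaining 28 days after active treatment, and λ what remains at visit 8 of active treatment given in period 1. Negative values are improvements.

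| | AP | PA |
|---|---|---|
| Visit 5 | d5 + τ | d5 |
| Visit 8 | d8 + λ | d8 + τ |

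Pooled over equal sequence groups, as mean change:

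- Visit 8 minus baseline: d8 + (τ + λ)/2. With d8 = −1.0 and τ = λ = 0, this is −1.0 although there is no treatment effect. With d8 = 0, τ = −1.5 and λ = 0, it is −0.75, half the true effect.
- Visit 8 minus visit 5 (the period 2 baseline), not relabelled by treatment: (d8 − d5) + [(λ − τ) + τ]/2 = (d8 − d5) + λ/2. The effect τ cancels completely.
- Visit 8 minus visit 7, with an on-treatment effect of −1.5 and no other change: if the effect wears off, (0 + 1.5)/2 = +0.75; if it persists fully, 0. The test would react when the effect has gone and not when it persists.

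Contrasts that do target treatment:

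- (a) Visit 8, PA minus AP: τ − λ.
- (b) Visit 5 minus visit 8, AP minus PA: (d5 − d8 + τ − λ) − (d5 − d8 − τ) = 2τ − λ. The period terms cancel, and half the shift is τ − λ/2, which equals τ when λ = 0.

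**4. Illustration by simulation.** Assumptions, not from the document: 43 per sequence, SD of a within-patient change 3.0, between-patient SD 7, λ = 0, 1,500 runs. Entries are the rejection rate at two-sided 5% and the mean estimate (mean differences).

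| Persisting effect; drift to visit 8 | Signed rank, visit 8 minus baseline | Rank-sum between sequences, visit 8 change | Signed rank, visits 5 and 8 labelled by preceding treatment |
|---|---|---|---|
| 0; 0 | 5.1%; 0.01 | 5.1%; −0.02 | 4.7%; −0.01 |
| 0; −1.0 | 85.1%; −1.00 | 4.7%; 0.00 | 4.2%; −0.02 |
| −1.5; 0 | 61.0%; −0.76 | 61.6%; −1.53 | 99.5%; −1.51 |
| −1.5; −1.0 | 99.8%; −1.74 | 59.9%; −1.49 | 99.4%; −1.50 |

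Signed rank on visit 8 minus visit 7 rejected in 58–62% of runs when a −1.5 on-treatment effect wore off, and in 4.5–5.9% when it persisted.

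**5. Precision of (a) and (b) under the same SD.** The standard error of a difference in mean change between sequences is 3.0 × √(2/43) = 0.65. In (a) this applies to τ directly. In (b) halving the shift halves it, to 0.32.

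**The case against.** The strongest defence has four parts.

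- **The SAP may settle it.** The article is condensed and defers detail. Silence on the visit 8 method would not be a finding. Here, however, the article does fix a method, the same tests as at end of treatment, and that method does not fit the visit. The SAP can still correct this, but the deferral does not make the sentence right.
- **A paired contrast is available.** Visit 5 mirrors visit 8, each nominally 28 days after a treatment period, and both collect the scores. A reader might infer that the follow-up result is uncomputable, or that visit 8 is the trial's only view of persistence. Neither is supported: visit 5 gives an equal off-treatment view after period 1, and a contrast of visits 5 and 8 labelled by preceding treatment behaves well in the simulation. What remains is that the article does not state this pairing and places the difference at visit 8.
- **Nobody says a pooled pre/post test will be run.** That is true. The wording about a shift between two groups may even hint at a two-sample comparison. The harm is conditional on a literal reading, and the simulated rejection rates depend on assumed SDs and drift. The absence of a pair at visit 8 does not.
- **The analysis is descriptive.** This stands in full. The primary model uses the 2-week and 6-week changes, and the text gives visit 8 no role in the hierarchical testing.

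**Conclusion.** The point holds and should be fixed, with limited reach. The article names one non-parametric test, a paired one, and applies it to a visit at which each patient has one value after both treatments. This follows from the visit schedule alone and needs no numerical assumption.

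If the sentence were applied to pooled changes from baseline, a persisting effect would be halved (equal groups, λ = 0) and any common drift would be added in full. How often that would mislead cannot be read from the document. Sample size, the primary conclusion and the hierarchical tests are untouched, so this is not a threat to the trial's main result.

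A reader might also infer that a group comparison at visit 8 describes the second-period treatment only. The design does not support that. Every patient has had both treatments by then, and the comparison estimates τ − λ, so anything left from period 1 is mixed in.

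**What to change.** Replace the visit 8 sentence, in the SAP and before unblinding, with one of the following.

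- **(a)** Compare visit 8 between the two sequence groups with a Wilcoxon rank-sum test and the two-sample Hodges-Lehmann estimate. Label it a sequence comparison that combines the effect of the most recent treatment with any residual first-period effect. State the expected numbers as an assumption: about 43 per sequence if 86 complete, up to 54 if all 108 attend.
- **(b)** Define an explicit off-treatment contrast of visits 5 and 8. Compute the within-patient visit 5 minus visit 8 difference, compare it between sequences by rank-sum test so that the period effect drops out, and halve the Hodges-Lehmann shift to obtain the treatment difference. State that this assumes no first-period effect remains at visit 8; otherwise half of it enters the estimate.

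The statement in Study objectives and outcomes about the follow-up visit should then refer to whichever contrast is chosen.

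The cost is wording only, since Table 2 already collects all these scores at both visits. Option (a) is less precise than a paired comparison: in the illustration it detected a persisting −1.5 in about 60–62% of runs, against more than 99% for the labelled visit 5/visit 8 pairing. Option (b) avoids most of that loss but needs both visits from each patient.
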